#### Sample Size Estimation

With 95% CI and 80% power, a sample size of 880 MWRA, 15 to 49 years, per arm is required to estimate an increase from 28.9% to 36.9% (ie, 8% increase) in the proportion of MCM uptake. The assumed design effect of 1.5 and a 7% nonresponse rate is accounted for in the sample size calculations [35].

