### Quantitative Component

#### Overview

A nonrandomized, quasi-experimental study design with intervention and control arms is proposed to assess the impact of implementing a complex delivery model of interventions on the voluntary uptake of MCMs in two rural districts of Sindh. Two sequential face-to-face household surveys will be conducted before and after the 12-month implementation of the interventions [33]. The surveys will document the changes over time in mCPR alongside other outcomes of interest, such as unmet needs and demands satisfied.

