#### Sampling and Recruitment Strategy

A two-stage random-sampling strategy will be employed to select the clusters and households with respondents (ie, MWRA, 15-49 years). A higher response rate has been projected, as the survey will be conducted at the field level on a face-to-face basis. The face-to-face method has been accredited in the literature as an effective way of eliciting a higher rate of response from target audiences [33]. Sampling will consider each cluster level as a stratum; each cluster will be comprised of 100 to 150 households in the catchment area of the health facility. Each cluster will be a primary sampling unit. At the first stage, clusters will be randomly selected from the sampling frame of each district. Each household will be a secondary sampling unit. At the second stage, 20 eligible households will be selected using systematic random sampling to reach the calculated sample size (ie, 880 MWRA, 15-49 years, per arm).

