#### Statistical Analysis of the Quantitative Component

The data will be collected using an Android app and will be uploaded in real time to the Aga Khan University server. Data cleaning will be performed by identifying errors and missing entries under the supervision of the senior data manager. Descriptive statistics will be used to estimate prevalence (ie, proportions) and frequencies of outcome indicators. A univariate difference-in-difference analytical approach will be used to estimate the effect of the interventions. In addition, a Blinder-Oaxaca decomposition analysis will be conducted to identify and quantify determinants of mCPR. Analyses will be done using Stata Statistical Software (version 16; StataCorp LLC). Weighted analysis will be performed by target age group for each cluster.

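### The 880 women per arm are sized for a comparison of two proportions, so the stated 80% power for 8 points does not apply to the planned difference-in-differences

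*Protocol article*

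**What the plan says.** Under Sample Size Estimation, the protocol article gives one change in one proportion as its target: "a sample size of 880 MWRA, 15 to 49 years, per arm is required to estimate an increase from 28.9% to 36.9" per cent, and the precision is given as "With 95% CI and 80% power". It adds: "The assumed design effect of 1.5 and a 7% nonresponse rate is accounted for in the sample size calculations".

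The Overview of the Quantitative Component describes an intervention and a control arm and says: "Two sequential face-to-face household surveys will be conducted before and after the 12-month implementation of the interventions". Under Statistical Analysis of the Quantitative Component, and in the abstract, the effect estimate is named: "A univariate difference-in-difference analytical approach will be used to estimate the effect of the interventions". The primary outcome is the modern contraceptive prevalence rate.

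Under Sampling and Recruitment Strategy, clusters are drawn at random in each district, and then "20 eligible households will be selected using systematic random sampling to reach the calculated sample size (ie, 880 MWRA, 15-49 years, per arm"). The text does not say whether the endline draws new clusters, returns to the same clusters, or re-interviews the same women. The sample size paragraph mentions neither the four-cell contrast nor any correlation between rounds.

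**The concern.** The article states a sample size, a power and an estimator, and the three do not fit together. A comparison of two proportions has two sources of sampling error. A difference-in-differences over two districts and two rounds has four, and with equal cell sizes and no correlation between rounds its variance is about twice as large. A size chosen to give 80% power for the first contrast therefore gives less for the second.

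This touches the primary outcome and the main effect estimate. A reader who takes the 80% at face value will believe the study can detect its 8-point target more reliably than it can, and will have the wrong detectable effect in mind when reading the interval around the result.

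**Working it through.** **Inputs from the article.** Proportions 0.289 and 0.369, 95% confidence, 80% power, design effect 1.5, nonresponse 7%, 880 per arm (Sample Size Estimation); 20 households per cluster (Sampling and Recruitment Strategy); two arms and two rounds (Quantitative Component, Overview).

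**Assumptions, not stated in the article.** Two-sided alpha of 0.05; 880 per arm in each round; design effect 1.5 and 7% nonresponse in all four cells; the control district stays at 28.9%.

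**Step 1: reproduce 880.** For two proportions, with mean 0.329 and binomial variances 0.289 × 0.711 = 0.2055 and 0.369 × 0.631 = 0.2328:

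- n = [1.96 √(2 × 0.329 × 0.671) + 0.8416 √(0.2055 + 0.2328)]² / 0.08² = 540 per group.
- 540 × 1.5 = 810, and 810 / 0.93 = 871.
- Rounding up to whole clusters of 20 gives 44 × 20 = 880. The 44 is my inference; it does not appear in the text.
- Check: effective n = 880 × 0.93 / 1.5 = 545.6. SE = √[(0.2055 + 0.2328) / 545.6] = 0.0283. Power = Φ(0.08 / 0.0283 − 1.96) = 80.6%.

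A one-sided 5% test gives about 683 to 728 per arm depending on the variant, so it does not reproduce 880.

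**Step 2: difference-in-differences, independent rounds.** Three cells at 28.9% and one at 36.9%:

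- Sum of variances = 3 × 0.2055 + 0.2328 = 0.8493.
- SE = √(0.8493 / 545.6) = 0.0395.
- Power = Φ(0.08 / 0.0395 − 1.96) = 52.7%. A simulation gave the same figure.
- Effect detectable with 80% power, solving d = (1.96 + 0.8416) × SE(d) iteratively: 11.1 points.
- Size for 80% power at 8 points: (1.96 + 0.8416)² × 0.8493 / 0.08² = 1,042 effective per cell; × 1.5 / 0.93 = about 1,680 per arm per round.

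**Step 3: same clusters, new women.** The article's own design effect limits how much this can help.

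- Implied intracluster correlation = (1.5 − 1) / (20 − 1) = 0.026.
- If the cluster effects persist completely, the correlation between the two rounds' district estimates is 20 × 0.0263 / 1.5 = 0.35.
- Variance with correlation ρ = [2 × 0.2055 × (1 − ρ) + 0.2055 + 0.2328 − 2ρ √(0.2055 × 0.2328)] / 545.6.
- At ρ = 0.35: SE = 0.0318, power = 71%, and the effect detectable with 80% power is about 8.9 points.

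**Step 4: power for 8 points by between-round correlation.**

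| ρ | Power |
|---|---|
| 0 | 53% |
| 0.1 | 57% |
| 0.2 | 62% |
| 0.3 | 68% |
| 0.35 | 71% |
| 0.5 | 82% |

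**Step 5: other readings, independent rounds.**

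- All 880 respond: 55.7%.
- Baselines from Table 1 (28.1% and 30.6%) with 8 points added: 52.5%.
- 880 as the total over both rounds, 440 per cell: about 30%.
- One-sided 5% test: about 65%.

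**The case against.** The strongest case on the other side is that 53% rests on four independent samples, and the article never says the samples are independent. It describes two sequential surveys and how clusters and households are drawn, but not whether the endline returns to the same clusters. If it does, the rounds are positively correlated and power rises. This stands: the result has to be given as a range conditional on the sampling, as in Steps 2 to 4. It does not rescue the 80%, because revisited clusters with new women reach at most about 71%.

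A second objection is that a full protocol or analysis plan may settle this. It may state the endline sampling. But the point is not an omission: the article itself attaches 80% to a contrast other than the one it says will estimate the effect. A later document could make the 80% true at this size only through a strong correlation that the article does not claim.

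Three stronger readings are tempting, and the article does not support them.

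- A reader might infer that 880 was miscalculated. It was not; it is sound for its own contrast.
- A reader might infer that the study simply has an even chance of detecting its target. That is one end of the range and depends on independent rounds.
- A reader might infer that a null result will be taken as evidence against integration. The article gives no decision rule and no rule for reading non-significance; it speaks of estimating the effect.

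**Conclusion.** The concern holds as a mismatch between sizing and analysis. The stated 80% power for 8 points belongs to a two-proportion comparison and does not carry over to the planned difference-in-differences. Under the assumptions listed in the working, power runs from about 53% with independent rounds to at most about 71% with revisited clusters and new women; the corresponding effects detectable with 80% power are about 11 and about 9 points.

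The 71% is an upper limit for new women: it treats the whole design effect as clustering and lets cluster effects persist fully. Following the same women, or re-selecting many of them by chance, would add correlation, and a value near 0.5 would be needed to restore 80%. No panel is described and no correlation is claimed. Taking 880 as the total over both rounds would make the shortfall larger.

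**What to change.** In Sample Size Estimation:

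- State whether the endline draws new clusters, revisits the same clusters, or re-interviews the same women, and whether 880 applies to each round.
- State the between-round correlation assumed.
- Restate power and the detectable effect for the difference-in-differences on that basis. Under independent samples the present assumptions give about 53% power for 8 points and 80% power for about 11 points.
- Replace the assumed prevalence, design effect and nonresponse with the values seen in the baseline survey completed in January 2021.

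The cost is a recalculation and a reworded paragraph. No extra respondents are needed, and the estimator does not change; the stated power becomes less favourable. The 1,680 per arm per round in Step 2 shows the size of the gap and is not a proposal, since the baseline round is already complete.

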#### Sampling and Recruitment Strategy

A two-stage random-sampling strategy will be employed to select the clusters and households with respondents (ie, MWRA, 15-49 years). A higher response rate has been projected, as the survey will be conducted at the field level on a face-to-face basis. The face-to-face method has been accredited in the literature as an effective way of eliciting a higher rate of response from target audiences [33]. Sampling will consider each cluster level as a stratum; each cluster will be comprised of 100 to 150 households in the catchment area of the health facility. Each cluster will be a primary sampling unit. At the first stage, clusters will be randomly selected from the sampling frame of each district. Each household will be a secondary sampling unit. At the second stage, 20 eligible households will be selected using systematic random sampling to reach the calculated sample size (ie, 880 MWRA, 15-49 years, per arm).

#### Outcomes

The primary outcome is the mCPR. The operational definition of the primary outcome can be found in Multimedia Appendix 3.

The secondary outcomes are as follows (see Multimedia Appendix 3 for their operational definitions):

Unmet needsDemands satisfiedProportion of women showing positive attitudes toward FP visits where clients received integrated FP-MNCH servicesProportion of referral completers who accepted an FP methodProportion of follow-up visits where clients received integrated FP-MNCH servicesPercentage of women who were satisfied with the services providedPercentage of staff scoring 70% or above on a knowledge assessment test using validated tools, at the facility and community levelsNumber of unwanted pregnancies and birthsProportion of married women who used ANC and PNC servicesProportion of institutional deliveries by skilled birth attendants.

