### Intervention Sites

The intervention will be implemented within existing health systems, including public and private health facilities, and among community-level health workers. The intervention duration will range from 12 to 18 months. Six public health facilities working under the Department of Health, 10 private health facilities, and all LHWs working in the catchment areas and along the referral pathway will be included in the Matiari district in Sindh (Table 2). A similar number of health facilities and outreach LHWs will be selected as control facilities and LHWs from the Badin district.

**Table 2 table2:** Health system characteristics of the study districts.

District	Type of health facility, n				Lady Health Workers, n		Target population, n
	Secondary	Primary	Private				
Matiari (intervention district)	3	3	10	144		269,304	
Badin (control district)	3	3	10	170		604,888	

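### Provider knowledge is listed as an outcome only as a pass rate at 70%; the numeric score behind it should be analysed alongside as a secondary outcome

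*Protocol article*

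**What the plan says.** In the protocol article, Outcomes names a single primary outcome: "The primary outcome is the mCPR". It then introduces the secondary list: "The secondary outcomes are as follows (see Multimedia Appendix 3 for their operational definitions". One item on that list is the percentage "of staff scoring 70% or above on a knowledge assessment test", assessed with validated tools among facility and community staff. No mean, median or full score appears as an outcome, and no reason is given for the value 70%.

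Statistical Analysis of the Quantitative Component plans proportions and frequencies for the outcome indicators and a univariate difference-in-difference for the intervention effect. As written, the analysis would therefore act on the pass rate.

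Intervention Sites says of Matiari that "all LHWs working in the catchment areas and along the referral pathway will be included", and that a similar number of facilities and LHWs will be selected from Badin. Table 2 gives 144 LHWs for Matiari and 170 for Badin, and 16 facilities in each district (3 secondary, 3 primary, 10 private). How many staff will sit the test is not stated.

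**The concern.** Capacity strengthening of providers is the first intervention component in both the Abstract and the section on key strategies. The pass rate is the only listed outcome that measures provider knowledge directly. When the mCPR result is read, a natural question will be whether the training raised knowledge, and this outcome is the obvious place to look.

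A pass rate answers that question with less precision than the score from which it is made. A rise from 40 to 65, or from 72 to 95, changes nothing. How far the rate moves for a given gain depends on how many staff happen to sit near 70. The household sample of women adds nothing here, because the people tested are staff. If the score is not named as an outcome now, any later use of it will look post hoc.

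**Working it through.** **1. The plan's own figure.** The only sample size in the article is for mCPR: "a sample size of 880 MWRA, 15 to 49 years, per arm is required". The inputs, from Sample Size Estimation, are 28.9% against 36.9%, two-sided 5% (inferred from the stated 95% CI), 80% power, design effect 1.5 and nonresponse 7%. With pooled variance and no continuity correction:

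n = [1.96·√(2·0.329·0.671) + 0.8416·√(0.289·0.711 + 0.369·0.631)]² / 0.08² = 541

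541 × 1.5 = 812 after rounding up. Allowing for nonresponse, 812/0.93 gives 873, or 812 × 1.07 gives 869. Both are close to 880, so the figure reproduces. It concerns women and mCPR. No sample size, pass rate, mean or SD is given for the knowledge test, so there is no stated figure for this outcome to reproduce.

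**2. Information lost by the cut.** Assume normal scores with the same SD in the groups compared (not in the documents). Let p be the proportion passing, c the standard normal quantile of p, and φ the standard normal density. For a small mean shift, the efficiency of the pass rate relative to the mean is

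E = φ(c)² / [p(1 − p)]

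For example, at p = 0.5: 0.3989²/0.25 = 0.637. At p = 0.9: 0.1755²/0.09 = 0.342.

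| Passing | Efficiency | Information lost |
|---|---|---|
| 50% | 0.637 | 36% |
| 40% or 60% | 0.622 | 38% |
| 30% or 70% | 0.576 | 42% |
| 20% or 80% | 0.490 | 51% |
| 10% or 90% | 0.342 | 66% |
| 5% or 95% | 0.224 | 78% |

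The smallest possible loss is 1 − 2/π = 36%, reached when the cut falls at the median. There is no matching upper limit: the loss keeps growing as the pass rate nears 0 or 100%.

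**3. Illustration in terms of power.** Take the Table 2 LHW counts as if all were tested (144 and 170), a true shift of 0.35 SD (assumed), a two-sided 5% test after the intervention, and no clustering.

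- Mean score: SE = √(1/144 + 1/170) = 0.1133 SD; 0.35/0.1133 = 3.09; power = Φ(3.09 − 1.96) = 87%.
- Pass rate, control 50%: the intervention rate is Φ(0 + 0.35) = 63.7%; SE = √(0.25/170 + 0.637·0.363/144) = 0.0555; 0.137/0.0555 = 2.47; power = Φ(2.47 − 1.96) = 69%.
- Pass rate, control 25%: 25% to 37.3%, power 65%.
- Pass rate, control 70%: 70% to 80.9%, power 62%.

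A shift of 0.4 SD gives the same pattern: 94% for the mean, against 80%, 72% and 46% at control pass rates of 50%, 70% and 90%.

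**The case against.** The strongest case on the other side has four parts.

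- **The operational definition is out of sight.** It is in Multimedia Appendix 3, which is not shown, and nothing in the article says the score will go unreported. This stands against a reading that a reader might draw, namely that the score is thrown away; the text does not show that. It does not remove the point, because the appendix is cited to define the outcomes listed, and the outcome listed is the pass rate.
- **A threshold has its own meaning.** The share of staff who reach a set standard is a different question from the average gain, and insensitivity to movement on one side of the cut is part of what a threshold measures. This stands. It is why the 70% indicator should not be demoted to a descriptive line: that would replace the investigators' question with another.
- **The sizes are assumed.** This stands too. Normality, equal SD and the 0.35 or 0.4 SD shifts are not in the documents. The LHW counts come from a table of district characteristics and are not said to be the number tested. Facility staff are left out of the illustration. It also compares the districts after the intervention only and ignores clustering, whereas the article plans a difference-in-difference.
- **Other outcomes also bear on the training.** Integrated services at follow-up visits, acceptance of a method among referral completers and women's satisfaction all say something about provider practice. It would therefore be too strong to call the knowledge test the only outcome that shows whether training worked. It is the only listed direct measure of provider knowledge.

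**Conclusion.** The point holds in a limited form. Provider knowledge is listed only as a pass rate although a numeric score must exist, and for detecting a mean shift the pass rate is the less precise of the two. Under roughly normal scores with equal SD, the loss is at least about 36%, about two thirds when 10% or 90% pass, and larger beyond that.

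A reader might infer that this trial will lose a third to two thirds of the information, or that its power will fall from 87% to between 62% and 69%. The documents support neither as a statement of fact. The first needs a pass rate between 10% and 90% as well as normality, and the second is an illustration on assumed inputs.

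The consequence is modest. This is one secondary outcome among several; the primary outcome, its sample size and the primary conclusion do not depend on it. It is a worthwhile improvement, not an error that threatens the trial.

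**What to change.** Keep the percentage at or above 70% as listed. Add to the secondary outcomes the continuous knowledge score (0-100), analysed in the same difference-in-difference between the two districts, using baseline scores where staff were tested before and allowing for clustering by facility. If the number of staff tested is known, state it in the same place.

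The cost is one sentence in the outcome list and one extra secondary analysis. No new data are needed, and the pass rate remains available for programme reporting.

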#### Statistical Analysis of the Quantitative Component

The data will be collected using an Android app and will be uploaded in real time to the Aga Khan University server. Data cleaning will be performed by identifying errors and missing entries under the supervision of the senior data manager. Descriptive statistics will be used to estimate prevalence (ie, proportions) and frequencies of outcome indicators. A univariate difference-in-difference analytical approach will be used to estimate the effect of the interventions. In addition, a Blinder-Oaxaca decomposition analysis will be conducted to identify and quantify determinants of mCPR. Analyses will be done using Stata Statistical Software (version 16; StataCorp LLC). Weighted analysis will be performed by target age group for each cluster.

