#### Selection of Control District

We used the propensity score matching technique to select the control district (Table 1). This procedure estimates the probability and propensity that a study unit that has not received the intervention is similar at baseline to another unit from the intervention group, based on a set of key characteristics. As such, it reduces the problem of comparison across large numbers of key variables [34]. In the context of our study, this matching was done to select Badin as the control district to compare with the intervention district of Matiari (Figure 1). The variables used in generating propensity score matching included CPR, mCPR, unmet needs, ANC by skilled providers, deliveries by skilled birth attendants, the Human Development Index, and percentage of full immunization coverage. The district-level data of these indicators were taken from the Sindh Multiple Indicator Cluster Survey 2018 for all 23 rural districts (Multimedia Appendix 2).

**Table 1 table1:** Selection of control district using propensity score matching.

District	Unmet needs, %	CPR^a^, %	Modern CPR, %	Fully immunized, %	Deliveries by skilled birth attendants, %	Antenatal care, %	Propensity score
Badin (control district)	17.9	28.1	28.1	45.6	61.9	82.0	0.36
Matiari (intervention district)	25.8	32.4	30.6	68.0	65.5	85.7	0.31

^a^CPR: contraceptive prevalence rate.

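### The effect estimate is fixed as an unadjusted difference-in-differences between two districts that still differ after matching; an estimate adjusted for individual and household covariates should be the main one

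*Protocol article*

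**What the plan says.** The section Statistical Analysis of the Quantitative Component, like the abstract, commits the effect estimate to one method: "A univariate difference-in-difference analytical approach will be used to estimate the effect of the interventions". No covariates are named. The two neighbouring sentences serve other purposes. The decomposition is there to explain prevalence: "In addition, a Blinder-Oaxaca decomposition analysis will be conducted to identify and quantify determinants of mCPR". The weighting is by age within cluster: "Weighted analysis will be performed by target age group for each cluster".

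The design is set out in the Overview of the Quantitative Component: "A nonrandomized, quasi-experimental study design with intervention and control arms is proposed". There is one household survey before the intervention and one after.

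Comparability is sought through district selection. Under Selection of Control District, "this matching was done to select Badin as the control district to compare with the intervention district of Matiari", using "CPR, mCPR, unmet needs, ANC by skilled providers, deliveries by skilled birth attendants, the Human Development Index, and percentage of full immunization coverage" from a 2018 survey. Table 1 prints six of these seven indicators and the scores. Table 2, titled "Health system characteristics of the study districts", gives Lady Health Worker counts and target populations.

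**The concern.** In a nonrandomized study with a single district per arm, the estimate rests on two conditions: that both districts would have followed the same trend without the intervention, and that the women sampled in each district are comparable from one round to the next. Matching was meant to support the first condition, and an unadjusted estimator does nothing for the second.

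The tables show that matching left sizeable gaps in unmet need, immunization coverage and probably Lady Health Worker density. These are not incidental characteristics. Unmet need is the pool from which new users come, and immunization contacts and Lady Health Workers are channels through which the intervention is delivered. Districts that differ on them could plausibly follow different trends.

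Separately, the Sampling and Recruitment Strategy section describes two-stage sampling of households and no follow-up of the same women. If each round is sampled afresh, any change between rounds in age, number of children, education or wealth that differs between districts enters the unadjusted estimate directly.

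**Working it through.** **1. The plan's own figure.** Inputs from Sample Size Estimation: 28.9% to 36.9%, 80% power, 95% confidence (two-sided 5% assumed), design effect 1.5, nonresponse 7%. The pooled two-proportion formula without continuity correction gives 541 per arm. Then 541 × 1.5 = 811.5, and 811.5 / 0.93 = 873 (or 811.5 × 1.07 = 869). The stated 880 is reproduced to within 3% and is used in step 5.

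**2. Gaps in Table 1 (2018 district data).**

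| Indicator | Matiari | Badin | Difference, points |
|---|---|---|---|
| Full immunization | 68.0% | 45.6% | 22.4 |
| Unmet need | 25.8% | 17.9% | 7.9 |
| CPR (any method) | 32.4% | 28.1% | 4.3 |
| Antenatal care | 85.7% | 82.0% | 3.7 |
| Skilled delivery | 65.5% | 61.9% | 3.6 |
| mCPR | 30.6% | 28.1% | 2.5 |

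The propensity scores are 0.31 and 0.36. Close scores do not guarantee that each indicator is close. Two of the six are far apart, and four, including the primary outcome, are not.

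**3. Lady Health Workers, Table 2.** Matiari: 269,304 / 144 = 1,870 people per worker. Badin: 604,888 / 170 = 3,558. The ratio is 3,558 / 1,870 = 1.9. This assumes that the counts and the populations cover the same area, which the article does not state.

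**4. What the estimator removes.** Write D = (Matiari after − Matiari before) − (Badin after − Badin before). A fixed level gap appears in both Matiari terms and drops out. What remains is the intervention effect, plus the difference in background trends, plus the difference between districts in how the sample composition changed. For a characteristic whose share of the sample shifts by an amount differing between districts by d, and whose carriers differ in method use by g, the last term is about d × g. With one round before the intervention, the planned surveys contain no earlier change against which to check equal trends.

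**5. Scale.** With 880 women per district per round and design effect 1.5, the effective size is 880 / 1.5 = 586.7. Under no effect at 28.9%, SE(D) = √(4 × 0.289 × 0.711 / 586.7) = 0.037, or about 3.7 points. For a trend difference b, the two-sided 5% test rejects with probability Φ(b/SE − 1.96) + Φ(−b/SE − 1.96):

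| Assumed trend difference, points | False-positive rate |
|---|---|
| 1 | 5.8% |
| 2 | 8.3% |
| 3 | 12.6% |
| 4 | 18.8% |

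The values of b are assumptions, as the documents give no district trends. The rejection rate rises slowly because the standard error is large, but the point estimate carries all of b.

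**The case against.** The strongest reply is that Tables 1 and 2 show levels, and a difference-in-differences subtracts levels. That is right: imbalance alone is not bias here.

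A reader might go further and infer that the estimate is biased upward, because Matiari has more unmet need and denser worker coverage and so would gain users anyway. The documents do not support this. They contain no district trends. Matiari, despite its apparent worker density, meets a smaller share of demand with modern methods: 30.6 / (32.4 + 25.8) = 52.6%, against 28.1 / (28.1 + 17.9) = 61.1% in Badin.

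A reader might also put a size on the bias by assuming that 10% to 30% of unmet need converts in both districts, giving 7.9 × 0.10 to 0.30 = 0.8 to 2.4 points. Those shares are high against the Background section. It reports CPR rising from 13% to 34% between 1990 and 2018, which is 21 / 28 = 0.75 points a year (the text gives 0.5). From January 2021 to September 2022 is about 1.67 years, so the gain is 0.8 to 1.25 points. Against national unmet need of 17% that is roughly 5% to 7%, and 7.9 × 0.05 to 0.07 is 0.4 to 0.6 points. This too is only indicative, being national and for any method.

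Nor can one conclude that the propensity model was inestimable with one treated district among 23. Complete separation would push the treated district's score towards 1, and Table 1 prints 0.31. The specification is in an appendix that is not shown.

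Age weighting may absorb part of an age shift, but not shifts in parity, education or wealth. It also cannot be said that the choice is merely left to an analysis plan, because the article itself states the univariate method.

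**Conclusion.** The point holds as a weakness in a stated method, not as a demonstrated bias. The article fixes an unadjusted effect estimate although its own tables show residual differences of 22.4 points in full immunization and 7.9 points in unmet need, and a 1.9-fold difference in people per Lady Health Worker if the bases agree. Differing trends and composition shifts would both pass into that estimate; neither their direction nor their size can be established from the documents.

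The conclusion on composition assumes that each round is sampled afresh, which the sampling text suggests but does not say outright. Adjustment for individual and household covariates can reduce that component. It cannot remove a trend difference between districts, because with one district per arm district and intervention coincide. The change should be made because it is cheap and addresses a specific source of error; it does not turn the comparison into a well-controlled one.

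**What to change.** Pre-specify as the main effect estimate a covariate-adjusted, survey-weighted difference-in-differences with standard errors robust to clustering at the primary sampling unit: modern method use on district, round and district × round, plus individual and household covariates of a pre-intervention kind, such as age, number of living children, woman's education and household wealth. Draw them from the covariates needed for the Blinder-Oaxaca analysis. Report the univariate estimate alongside.

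Do not adjust for Lady Health Worker coverage measured during the intervention, and do not interact it with round. These workers deliver the intervention, so such a term could absorb part of its effect. At most, use baseline coverage in a sensitivity analysis.

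Describe the Table 1 and Table 2 gaps as residual imbalance after matching, and state that a district-level trend difference cannot be separated from the intervention effect with one district per arm. If earlier district surveys are available, show pre-intervention trends from them.

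The cost is analysis wording and a little code, with no added sample, provided that the covariates were collected in the completed baseline survey (its questionnaire is not shown). The downside is a few more model terms and some dependence on the covariates chosen, which is why they should be named before the endline data are examined.
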